#### Subgroup analysis

Patients will be divided into subgroups according to the side of surgery. Subgroup analysis will be conducted to further explore the effect of our trial intervention on intraoperative oxygenation. Post-hoc analysis will be applied for subgroup analysis.

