### Sample size calculations

The primary endpoint of this study is oxygenation index measured at T4. According to literature [16], oxygenation index for patients inhaling pure oxygen and under well oxygenated conditions during TLV usually ranges between 350-400 mmHg and drops to 150-200 mmHg after patients are switched to OLV. Therefore, during OLV, changes in oxygenation index within the limit of 50 mmHg would be clinically insignificant. Thus, the cut-off value for inferiority is set to 50 mmHg. In other words, in our study, if oxygenation index measured at T4 of the study group is below that of the control group, but the difference between that of the two groups is within 50, then the ventilation strategy of the study group is not inferior to that of the control group in terms of improving intraoperative oxygenation. We set probability of type 1 error at α = 0.025, probability of type 2 error at β = 0.20, and power value at 0.80; a sample size of 38 is calculated for each group by using PASS 11.0 software. Considering a 10% removal and dropout rate, a final sample size of 42 is required for each group.

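### The side-of-surgery subgroup is planned in advance but labelled post hoc, and splitting patients by side does not test whether the effect differs between sides

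*Protocol article*

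**What the plan says.** The Subgroup analysis section has three sentences. The first fixes the factor: "Patients will be divided into subgroups according to the side of surgery". The second gives purpose and outcome area: "Subgroup analysis will be conducted to further explore the effect of our trial intervention on intraoperative oxygenation". The third reads "Post-hoc analysis will be applied for subgroup analysis".

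Trial status dates the protocol version (V1.0) 25 January 2024 and plans first enrolment for 1 March 2024. Study visits and data collection lists side of surgery among the recorded intraoperative items.

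For between-group comparison of a continuous outcome, Statistical analysis lists the independent-samples t test and the Mann–Whitney U test, with P < 0.05 as the threshold. Sample size calculations states "The primary endpoint of this study is oxygenation index measured at T4" and sets the margin for the trial as a whole: "Thus, the cut-off value for inferiority is set to 50 mmHg".

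**The concern.** There are two faults in what is written.

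First, an analysis whose factor and outcome area are set in a protocol dated before enrolment is not post hoc. The other possible meaning, post-hoc pairwise comparison after an omnibus test, does not fit a factor with two levels. Left as it stands, the label invites readers to discount a planned analysis as data-driven.

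Second, dividing the patients and applying the listed two-group tests answers whether there is an effect on the left and whether there is one on the right. It does not answer whether the two effects differ, which is what a subgroup analysis is for. Each side holds roughly half the patients, so one side can cross a threshold and the other miss it by chance alone. That pattern could then be reported as a side-specific effect.

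**Working it through.** **Inputs from Sample size calculations.** Margin 50 mmHg; alpha 0.025 (taken as one-sided, because the design is non-inferiority); power 80%. The evaluable size before allowance for dropout is 38 per arm.

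**Assumptions, not in the article.** The SD, a true difference of 0 for sizing, and the left/right split. Differences are study minus control, so negative values favour control.

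**1. Back-solving the SD.** The stated 38 cannot be reproduced directly because no SD is given. With n = 2 × SD² × (1.960 + 0.842)² / 50² and SD = 77:

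2 × 5929 × 7.849 / 2500 = 37.2, rounded up to 38.

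SDs of 76.8 to 77.7 mmHg return 38 by the normal formula, and 75.8 to 76.7 by the t distribution. SD 77 is used below.

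**2. Each side judged against 50 mmHg (a hypothetical use).** With an equal split there are 38/2 = 19 per arm per side.

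- SE of a side-specific difference = 77 × √(2/19) = 25.0 mmHg.
- Power per side at true difference 0 = Φ(50/25.0 − 1.96) = 51.7%; by the noncentral t, 49.5%.
- Chance that exactly one side meets the margin = 2p(1 − p) = 2 × 0.517 × 0.483 = 49.9%; by t, 50.0%.
- Simulation (200,000 runs): exactly one side 49.8%, both 24.8%, neither 25.4%.

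This follows from halving the sample. If n gives 80% power at a true difference of 0, half of n gives Φ(2.80/√2 − 1.96), about 51%, whatever the SD.

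**3. The listed test within each side (difference, two-sided P < 0.05).** With no effect, each side is significant with probability 0.05. Exactly one is significant in 2 × 0.05 × 0.95 = 9.5% of trials.

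**4. Dependence on the common true difference** (normal approximation, SD 77, 19 per arm per side). Percentage of trials in which the two sides disagree:

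| True difference, both sides (mmHg) | Judged against margin | Listed two-sided test |
|---|---|---|
| −50 | 5% | 50% |
| −25 | 28% | 28% |
| −10 | 46% | 13% |
| 0 | 50% | 9.5% |
| +10 | 44% | 13% |
| +25 | 25% | 28% |
| +50 | 4% | 50% |

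**5. Other ranges for the margin-based figure at true difference 0.** Splits from 55:45 to 70:30 give 50% to 56%. With 42 per group and an equal split it is 49% to 50%. With n held at 38 and a different true SD: 23% at SD 50, 40% at 60, 48% at 70, 45% at 100.

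**6. What an interaction term would deliver.** SE = 77 × √(4/19) = 35.3 mmHg. The 95% half-width is 1.96 × 35.3 = 69 mmHg, or 70 mmHg with the t multiplier of 1.99. The left–right difference detectable with 80% power is 2.80 × 35.3 = 99 mmHg, and power for a 50 mmHg difference is about 29%. Tested at two-sided 0.05, the interaction would falsely signal a difference between sides in 5% of trials with identical effects.

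**The case against.** The strongest reply has four parts.

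- **The margin is never applied by side.** The section says only that oxygenation will be explored further. This stands. A reader might infer that the two sides will reach opposite conclusions about half the time, but the documents do not support that. The 50% needs a within-side verdict against 50 mmHg that is not planned, plus a true difference near 0. Also, a side that fails to meet the margin has not been shown inferior, so the conclusions would differ without being opposite.
- **The figures rest on inputs the article does not give.** This also stands for the SD and the left/right split. They are assumptions, and the ranges above belong with any number quoted.
- **The post-hoc label causes none of this disagreement.** Correct. The disagreement comes from splitting the sample, and removing the label would not change it. These are two separate faults in one short section.
- **An interaction model may sit in a full protocol or SAP that is not shown.** It may, and its absence from a condensed article is not by itself a fault. This stands only in part. The article states a method, dividing the patients, and the between-group tests it lists fit only within-side comparisons. That stated method does not serve the purpose of a subgroup analysis. The label, too, is a misstatement that no further detail would repair.

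**Conclusion.** The point holds in a limited form. The post-hoc label contradicts a subgroup set out in the protocol. The analysis as described compares groups within each side and does not test whether the effect differs by side.

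The size of the risk depends on how the side-specific results are used. It is about 10% under the listed two-sided test with no effect, and about 50% if each side were held to the 50 mmHg margin at a true difference of 0, with SD about 77 mmHg and equal sides. Both vary widely with the common true effect, and the second describes a use the article does not announce.

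Even the right contrast would be imprecise, with a 95% half-width of about 70 mmHg against a margin of 50 mmHg. The analysis can therefore only be exploratory. Severity is low: the primary conclusion and the sample size are unaffected.

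**What to change.** Delete the post-hoc wording and call this a prespecified exploratory subgroup analysis. State that one model will be fitted for the T4 oxygenation index with treatment, side and treatment-by-side. Report the interaction estimate with its 95% CI beside the two side-specific differences, and state that no non-inferiority claim will be made within a side. If the SAP already contains such a model, align the protocol wording with it.

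The cost is a sentence or two and one model term. Side of surgery is already recorded, so no new data or patients are needed.

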## Discussion

Although atelectasis formation during anesthesia induction is difficult to avoid, it may have little influence on patients during one lung ventilation. Subjects of this trial are intubated in supine position before being switched to lateral decubitus position to receive one lung ventilation. In supine position, the pressure imposed by the lungs’own weight results in the reduction of trans-pulmonary pressure by 0.25cmH_2_O for every 1 cm on the ventral to dorsal axis. In consequence, for patients receiving mechanical ventilation in supine position, the dorsal parts of lungs are prone to collapse due to the reduction of trans-pulmonary pressure along the gravitation axis [17]. Tusman and colleagues discovered that by switching the body position of anesthetized children from supine to the left and subsequently right lateral decubitus position lasting 90 s each could recruit the collapsed alveoli in the dorsal parts of the lungs [18]. Mikulas and colleagues found that by tilting the less aerated lung of patients receiving mechanical ventilation for COVID-19-associated ARDS up 30˚ in combination with a decremental PEEP titration procedure could alleviate the degree of atelectasis [19].

When patients are placed in lateral decubitus position, the lower flank of the dependent lung is prone to collapse due to the impact of gravitational force. In our study, patients randomized to the group without RM receive one lung ventilation followed by immediate PEEP titration right after being placed in lateral decubitus position before the formation of atelectasis in the lower flank of the dependent lung. However, in most previous studies, patients received two lung ventilation without PEEP and inhaled pure oxygen after being placed in lateral decubitus position, and thus were prone to form atelectasis rapidly [1, 3–6]. Furthermore, in those studies, one lung ventilation was initiated after pleura opening and then patients received PEEP alone or received RM followed by iPEEP titration or a fixed level of PEEP. Hence, most previous researches compared the effects of PEEP applied alone or in combination with RM after the formation of atelectasis.

Recruitment maneuver could lead to temporal hemodynamic instability. Hence, the ideal recruitment maneuver eliminates atelectasis with the lowest effective peak inspiratory pressure and fewest numbers of breaths or shortest effective time [20]. Yet, evidence on the effective time and effective peak inspiratory pressure during recruitment maneuvers are still lacking. Although, the advantages of individualized PEEP has been proven by numerous studies, recruitment maneuvers applied in the majority of studies are unindividualized. Wu and collegues compared the effects of traditional recruitment maneuvers and ultrasound guided recruitment maneuvers on patients undergoing thoracic surgery [21].They discovered that, the incidence and severity of atelectasis are lower in patients receiving ultrasound guided recruitment maneuvers than those receiving conventional recruitment maneuvers. Therefore, unindividualized recruitment maneuvers may not be effective in recruiting all collapsed alveoli and thus has limited benefit. On the other hand, the pressure and time of unindividualized recruitment maneuvers may be excessive, aggrevating its potential harm.

Ideally, satisfactory collapse of the independent lung would be achieved to facilitate surgical procedure, while the atelectasis of the dependent lung is minimized to improve oxygenation and ventilation mechanics. Inhaling pure oxygen would facilitate the development of atelectasis, which plays a key role in the phase II collapse of the independent lung [22]. On the other hand, limiting the fraction of inspired oxygen could alleviate atelectasis [20].Thus, before placing the patient in lateral decubitus position, we lowered the fraction of inspired oxygen during ventilation of the dependent lung to avoid formation of atelectasis during adjustment of the position of the double lumen tube which necessities temporal disconnection from the ventilator. While the independent lung is ventilated with pure oxygen to facilitate the development of atelectasis.

The pressure required to open up collapsed alveoli is far higher than that needed to prevent atelectasis formation. So, if PEEP is incrementally titrated, atelectasis usually develops before PEEP reaches the level sufficient to prevent alveoli from collapsing, and thus limits the benefits of PEEP. Spadaro and colleagues discovered that during one lung ventilation, PEEP obtained via both decremental and incremental titration procedures could reduce intrapulmonary shunt, but only PEEP titrated decrementally succeeded in reducing driving pressure and improving oxygenation [24]. Chuimello and colleagues found that during a stepwise decremental PEEP titration procedure, keeping PEEP constant for 5 min at each step was adequate for arterial partial pressure of oxygen, oxygenation index, venous admixture and arterial blood oxyhemoglobin saturation to reach equilibrium [23]. In contrast, during a stepwise incremental PEEP titration procedure, keeping PEEP constant for more than 60 min was insufficient for the aforementioned parameters to reach equilibrium [24]. In the majority of studies, during a PEEP titration procedure, iPEEP was selected based on parameters associated with oxygenation and respiratory dynamics. In addition, in numerous studies, PEEP was kept constant for 40 s to 3 min after each step of a stepwise decremental or incremental PEEP titration procedure, which was far shorter than the time required for paremeters including oxygenation index to reach equilibrium [4, 5, 14, 23]. In conclusion, acquiring PEEP from an incremental PEEP titration procedure is inappropriate.

One lung ventilation could result in injury of both the independent and the dependent lung [25]. According to literature, during one lung ventilation, apneic oxygen insufflation to the independent lung at a fixed rate of 5L/min could retain a degree of its expansion, which not only contributes to mitigated inflammatory reaction but also alleviates the anoxic-reoxygenation injury acquired after the end of one lung ventilation [26]. Therefore, we will apply apneic oxygen insufflation to the independent lung at a constant rate of 5L/min to minimize the effects of its injury on the incidence of PPCs. Although surgery-related lung injury is beyond control, according to literature, detriment caused by ventilator-associated lung injury is far greater than that caused by surgical trauma [27]. Thus, surgery-related lung injury has no profound impact on the outcome of this study.

## Trial status

The protocol version is the first version (No. V1.0/2024.01.25). We will enroll the first participant of the trial on March 1, 2024, and complete recruitment on September 30, 2025.

## Data Availability

The datasets supporting the conclusions of this article are included within the article and its additional files.

## Abbreviations

ARDS: Acute respiratory distress syndrome
PPCs: Postoperative pulmonary complications
iPEEP: Individualized positive end-expiratory pressure
Cstat: Static lung compliance
FiO_2_: Fraction of inspired oxygen
RM: Recruitment maneuvers
V_T_: Tidal volume
CRF: Case Report Forms
BMI: Body mass index
CPAP: Continuous positive airway pressure
V/Q: Ventilation perfusion ratio
COPD: Chronic obstructive pulmonary disease
Pplat: Plateau airway pressure
Ppeak: Peak airway pressure
1:E: Ratio between inspiratory and expiratory time
PaCO_2_: Partial pressure of arterial carbon dioxide
PaO_2_: Partial pressure of arterial oxygen
ACEI: Angiotensin converting enzyme inhibitor
ARB: Angiotensin receptor blocker
DLT: Double lumen tube
OLV: One lung ventilation
Qs/Qt: Fraction of intrapulmonary shunt
TOF: Train of four
MAP: Mean arterial pressure
SIMV: Synchronized intermittent mandatory ventilation
PCV-VG: Pressure controlled volume guaranteed mode
AOI: Apneic oxygen insufflation
TLV: Two lung ventilation
FEV1: Forced expiratory volume in one second
FVC: Forced vital capacity
ALT: Alanine aminotransferase
AST: Aspartate aminotransferase
